## 10. TRIAL DRUGS

### 10.1. Formulation

The investigational product, TKM-130803 Injection is presented as an aqueous dispersion of nucleic acid/lipid particles (also referred to as Lipid Nanoparticles, LNP) in a 10 mL United States pharmacopeia (USP) Type I borosilicate glass vial with a Fluorotec®-faced butyl rubber stopper and an aluminum flip-off cap. TKM-130803 is a formulation of siEbola-3 drug substance with lipid excipients. The nucleic acid/lipid particles (LNPs) have an average size of approximately 60 to 90 nm.

The nominal mg/mL drug concentration of the specific batch of TKM-130803 will be recorded on each vial and also on the corresponding storage cartons. **TKM-130803 vials should remain in the cartons protected from light and stored refrigerated at 2 to 8°C (35.6 to 46.4°F). DO NOT FREEZE.**

TKM will be administered by a two hour IV infusion. The patient will receive 150mL of TKM-130803 dosing solution in 0.9%NaCl. An infusion pump should be used when administering TKM-130803 to ensure a well-controlled rate of infusion.

For full details of infusion preparation and administration please refer to the relevant trial Standard Operating Procedure manual.

## 10.2. Storage and Accountability

TKM vials should be stored refrigerated at 2 to 8°C (35.6 to 46.4°F). They must not be frozen.

Inventory, dispensing and accountability of study treatment will be tightly controlled. Treatment dispensed to the Confirmed ward, but not consumed by patients will not be returned due to infection control procedures and will be destroyed. Full accountability procedures and logs will be detailed in the corresponding study reference SOPs.

## 11. SAFETY REPORTING

Due to the nature of the symptoms of EVD (see **Table 2**) and the relatively small sample size it will be very difficult to differentiate between symptoms of the disease and events due to treatment, and the trial will have limited power to do this. Our investigation of safety will therefore focus on Serious Adverse Reactions (SARs) and Suspected Unexpected Serious Adverse Reaction (SUSARs) and key adverse events [e.g. diarrhoea, vomiting, bleeding, allergic reaction, anaphylaxis, cytokine release, flushing, hypotension and pain (chest pain, back pain, abdominal pain and headache)]. We will collect data using the CRF on these symptoms if they are new or worsening including, as far as possible, a severity grading in line with the CTCAE (Common Terminology Criteria for Adverse Events). These will only be reported to TOG/IDMC in accordance with the safety reporting as described below.

### 11.1. Definitions for safety reporting

**Serious Adverse Reaction (SAR)** – A serious untoward and unintended response in a participant to the study treatment, which is related (or has a reasonable possibility of being related) to any dose administered to that participant.

To qualify as “serious” the response must meet one of the following criteria:

- results in death
- is life-threatening
- requires inpatient hospitalisation or prolongation of existing hospitalisation
- results in persistent or significant disability/incapacity
- consists of a congenital anomaly or birth defect.

Other ‘important medical events’ may also be considered serious if they jeopardise the participant or require an intervention to prevent one of the above consequences.

For this protocol, due to the expected high death rate due to EVD, medical events that are not considered related to any dose of study treatment are *not* considered to be Serious Adverse Events (SAEs).

**Suspected Unexpected Serious Adverse Reaction (SUSAR)** - A serious adverse reaction, the nature and severity of which is not consistent with the information about the medicinal product in question set out in the investigator's brochure (IB).

### 11.2. Procedures for safety reporting

All SARs will be reported by the site to the operational team within 48 hours. In discussion with the site staff, the operational team will assess the SAR for expectedness and relatedness and report all SUSARs to the independent data monitoring committee (IDMC) immediately. The operational team will also report any SARs and SUSARs to all the relevant parties (such as IRBs, regulatory authorities and Tekmira) as required within 7 days.

Evaluation relatedness of reactions will consider the opinion of the site staff and the expected signs, symptoms and events associated with Ebolavirus disease or trial treatment according to the relevant Investigators' Brochure. Evaluation of expectedness will be made with reference to the Investigator's brochure. Serious infusion reactions will be reported. While the clinical syndrome of cytokine release may mimic other symptoms of EBOV, if suspected and serious, it will be reported to the TOG/IDMC.

**Table 2.** Symptoms of Ebolavirus disease (WHO Ebola Response Team, 2014; ISARIC WHO Viral Haemorrhagic Fever CRF)

| Known symptoms and clinical events of EVD: |                                  |
|--------------------------------------------|----------------------------------|
| Death                                      | Coma or unconsciousness          |
| Fever                                      | Unexplained bleeding             |
| Fatigue                                    | Hematemesis                      |
| Loss of appetite                           | Blood in stool                   |
| Vomiting                                   | Bleeding gums                    |
| Diarrhoea                                  | Bloody nose                      |
| Headache                                   | Bloody cough                     |
| Abdominal pain                             | Other bleeding                   |
| Joint pain                                 | Bleeding at injection site       |
| Muscle pain                                | Blood from vagina                |
| Chest pain                                 | Blood in urine                   |
| Cough                                      | Bleeding under the skin/bruising |
| Difficulty breathing                       | Back pain                        |
| Difficulty swallowing                      | Decreased urine output           |
| Conjunctivitis                             | Lower chest wall indrawing       |
| Sore throat                                | Hearing impairment               |
| Confusion                                  | Tinnitus                         |
| Hiccups                                    | Seizures                         |
| Jaundice                                   | Hepatomegaly                     |
| Eye pain                                   | Splenomegaly                     |
| Rash                                       | Lymphadenopathy                  |

## 12. STATISTICS

## 12.1. Description of Statistical Methods

The trial is designed to determine whether TKM is a promising treatment for Ebola. No early stopping in the case of evidence of efficacy is proposed, as there are currently only 100 courses of TKM available so early general roll out of the treatment is not possible. Enrolling the full 100 patients will maximize the precision of the final estimate of efficacy.

A futility design (Whitehead and Matsushita, 2003) is therefore used to allow early stopping in the event of evidence of futility or harm. This approach will recruit up to 100 patients, but will stop if the number of successes observed so far falls below a certain threshold.

In order to avoid early stopping due to enrollment of patients with very severe, late Ebola virus disease, who may not be expected to be salvaged even by an effective antiviral therapy, the stopping rule will be calculated after exclusion of enrolled patients who die within 48 hours of admission to the ETU.

For the purposes of determining futility, the effectiveness of the treatment will be judged in terms of the probability that a patient allocated to TKM treatment will survive to D14, after excluding patients who die within 48 hours of admission to the ETU. This probability will be denoted by  $p$ . Note that  $p$  represents the true value of the probability rather than any estimate that might be found from the trial data. The value  $p = 0.55$  will be used for guidance. If  $p \leq 0.55$ , then the treatment will be regarded as 'not promising' and the trial will be terminated.

The choice of guide value for  $p$  has been made following an analysis of individual level data on patients from a Ebola Treatment Centres from this current outbreak at Gueckedou, Foya, Kailahun and Elwa 3. Data on the outcomes of 1592 patients with laboratory confirmed Ebolavirus infection from these four centres are shown in Table 3. Only data from adults have been included, and data on patients who died on the day of admission or on the following day, or else the day after that have been omitted.

**Table 3:** Estimates and 95% confidence intervals for the probability of surviving to Day 14 following admission to the treatment centre, excluding patients who die on the date of admission or on the day after or the day after that. Success is taken to be a difference between the date of death and the date of admission that is  $> 13$  days.

|             | Gueckedou | Foya  | Kailahun | Elwa 3 | Overall |
|-------------|-----------|-------|----------|--------|---------|
| Lower limit | 0.485     | 0.428 | 0.514    | 0.510  | 0.517   |
| Estimate    | 0.535     | 0.495 | 0.568    | 0.554  | 0.543   |
| Upper limit | 0.585     | 0.562 | 0.622    | 0.598  | 0.569   |

As a result of this analysis,  $p = 0.55$  has been set as the success rate threshold above which TKM would be considered promising.

While children are initially excluded from the TKM arm of the trial, if the eligibility criteria is expanded to age  $>5$  following IDMC review of preliminary results, TKM trial data from adults and children will be jointly analysed, since the availability of TKM is restricted to 100 treatment courses and a stratified analysis is infeasible. Case fatality is highest in children aged  $< 5$  years, after which it declines with age reaching a minimum in persons aged about 15-20 years. Therefore the inclusion of subjects aged 5-17 years is not expected to inflate the case fatality, and the futility threshold of  $p \leq 0.55$  is expected to remain valid.

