### 5.2. Safety and tolerability

TKM-130803 has the same formulation as TKM-100802 except for two nucleotide swaps in the VP35 siRNA and a single nucleotide swap in the L-pol siRNA. Therefore the safety and tolerability profile is expected to be similar to TKM-100802. For a detailed description of the safety and tolerability of TKM-100802, please refer to the Investigator Brochure and additional safety summary. Adverse events (AEs) considered most likely to occur with TKM-130803 include discomfort, bruising, and bleeding at the site of infusion, and adverse effects analogous to those observed in animal studies, including coagulopathies, renal impairment, hepatobiliary injury and acute phase reaction.

In a human single ascending dose trial of TKM-100201 administered over one hour to healthy participants, infusion-related reactions, notably cytokine release syndromes (CRS) were observed. Clinical manifestations included flushing, headache, fever, hypotension, chills, nausea, and vomiting. Most of the reported treatment related AEs were consistent with a transient inflammatory response that begins within 6 hours after infusion and dissipates in most cases by 24 hours post-dosing. This interpretation is consistent with laboratory findings of transient elevations in some cytokines (e.g., MCP-1, IL-6, IL-1ra, IL-8) in some patients measured 2 and 6 hours post-dosing, returning to at or near baseline levels by 24 hours. In

addition, focal and reversible pain has been observed in association with liposomal or LNP therapeutics, particularly in the back, sacrum and sternum.

Fertility and reproductive toxicity studies have not been performed with TKM-100802 or TKM-130803.

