## **7.4. Trial enrolment**

Trial enrolment and allocation to treatment or observational cohort will take place as described in Figure 2 and below.

1. All ETC patients with a laboratory confirmed case of EBOV who can tolerate trial procedures and in whom IV access is possible will be eligible for randomisation into the observational trial.

Patients who are for end of life care only, or who are a late transfer from another facility (and already recovering from EVD) will not be eligible.

2. Patients will also be assessed for eligibility for drug allocation according to the criteria in section 7.3.
3. Allocation into this drug eligible cohort will occur by the following process.
  - i. Following arrival of the trial staff each morning, the maximal number of study beds (b) available for patients to receive study drug will be determined by the ETC clinical lead and the trial clinical lead.
  - ii. Whenever possible, patient dosing will be started within 2 hours of the trial team arrival in the morning, in order to provide adequate time for patient monitoring and to complete the required assessments during the working day. Consent and any randomisation will need to be completed before this time. If a patient chooses to delay consent, or consent cannot be obtained e.g. family or proxy not available, consent and randomisation of other patients will proceed. Any patients who cannot consent will be considered for enrolment the following day if this is still within the required 48 hour window, see Section 8.1.
  - iii. Following consent of patients who have arrived with or received PCR confirmation in the preceding 48hrs, each patient eligible for TKM-130803 treatment will be randomly allocated a number (n) from 1 to N, where N is the number of patients eligible (using a random number allocation program code in R statistical software).
  - iv. Patients will be allocated to the treatment cohort by sequentially selecting patients by their number (n) from 1 to b. The remainder of patients will be put forward for the observational cohort (when  $N > b$ ).
  - v. If on the calendar day of randomisation a patient allocated to TKM-130803 treatment is unable to receive treatment (e.g. because they refuse, die, or IV access cannot be obtained), the next patient in the sequence may be entered in to the treatment arm. This may only occur on the calendar day of randomisation.
  - vi. Re-randomisation to receive study drug is not permitted.

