## **8. TRIAL PROCEDURES**

### **8.1. Screening and informed Consent**

Patients with RT-PCR confirmed Ebolavirus RNA (confirmed patients) will be screened for trial eligibility and invited to give informed consent to participate, according to the procedures outlined in section 15.2. Staff will not discuss informed consent with patients (or the parents/representatives of patients <18 years old) who are not eligible for enrolment in any trial arm. The number of patients who are ineligible will be recorded anonymously. Study dosing, sampling and data collection will begin only after enrolment.

A patient may be consented to take part in the study anytime within 48 hours of first arriving at the ETC with a confirmed diagnosis, or, within 48 hours of being informed of Ebolavirus positive PCR result, if this occurs while already at the centre. Therefore, if a patient has been excluded for a reason that resolves within this period, they may be approached upon resolution of the reason for exclusion. If a patient wishes to delay their decision regarding consent, they may consent at any time within the 48 hour period.

Whenever possible, patient dosing will be started within 2 hours of the trial team arrival in the morning, in order to provide adequate time for patient monitoring and to complete the required post dose assessments. The actual time of dosing will depend on various factors, including number of patients on the study and staffing levels in the ETC. Consent and any randomisation will need to be completed before this time. If a patient chooses to delay consent, or consent cannot be obtained e.g. family or proxy not available, consent and randomisation of other patients will proceed. Any patients who cannot consent will be considered for enrolment the following day if this is still within the required 48 hour window.

A list of eligible patients will be produced each day (following receipt of the laboratory results).

Once the randomisation process is complete, to either the TKM treatment or observational cohorts, re-randomisation is not permitted.

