### 12.3. Criteria for the Termination of the Trial

Research sites will inform the data management centre every time that a patient is allocated to TKM treatment. Fourteen days after admission, they will report to the data management centre whether that patient did, or did not, survive to D14. Every time that a D14 report is received on a patient, a point will be plotted on Figure 5. This is plot of the number of survivals (S) reported so far against the number of D14 reports received (n), after excluding from both S and n those patients allocated to TKM treatment who died within 48 hours of admission. The plot is compared with the lower red boundary shown. If the plot reaches this boundary, the trial will be stopped with the conclusion that treatment with TKM is not promising. This safety plot will ensure a rapid reaction if TKM proves to be ineffective or harmful in the short term.

If the plot continues above the boundary until the green boundary is reached, corresponding to D14 reports being received from 100 patients, then it will be concluded that TKM is a promising treatment. If the trial has to be terminated before 100 patients have received TKM and before the lower red boundary is reached, and if stopping is due to a shortage of eligible patients rather than to any safety concerns, the final dataset will be analysed. If the outcomes of patients recruited are good enough it remains possible for TKM to be found promising, even following an incomplete study. Nevertheless, every effort will be made to complete the study of 100 patients if the lower boundary is not crossed and no important safety concerns emerge.

**Figure 5.** The stopping rule for the trial

[figure not shown]

The properties of the design have been calculated exactly, based on the independent Bernoulli distributions of each patient outcome. These are shown in Table 4 and depict the specified probability of reaching the most appropriate conclusion for a range of values of  $p$ . It can be seen that the probability is declaring TKM to be promising is set at 0.025 according to this design. Recommending a treatment associated with such a low probability of survival to D14 would be considered a type I error, and the risk

of this has been set at the conventional value of 0.025. The power of correctly identifying TKM as promising when  $p = 0.70$  is 0.827.

**Table 4:** Probabilities of claiming that TKM is promising for the phase II trial of Treatment TKM

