#### 12.5. Inclusion in Analysis

It is important to note that the primary sequential analysis described uses only data from patients who were admitted more than 14 days previously. Although it may be known that some more recently recruited patients have already died, their data will not yet be used, to avoid bias due to information on death being available sooner than information on survival. Enrolled patients who die within 48 hours of admission to the ETU will be excluded from the analysis.

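### Deaths within 48 hours of admission leave the monitoring plot even when they follow a dose, so the plot has a blind spot for early post-dose harm

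*Supplement*

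**What the plan says.** All references are to the latest protocol, v2.9.

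- **Exclusion.** Section 12.1: "the stopping rule will be calculated after exclusion of enrolled patients who die within 48 hours of admission to the ETU". Section 12.3 plots survivals S against reports n "after excluding from both S and n those patients allocated to TKM treatment who died within 48 hours of admission". Section 12.5 repeats it for the analysis: "Enrolled patients who die within 48 hours of admission to the ETU will be excluded from the analysis". None of the three distinguishes patients who have been dosed from those who have not.
- **Reason given.** Section 12.1 refers to very severe, late disease in patients "who may not be expected to be salvaged even by an effective antiviral therapy".
- **Purpose claimed for the plot.** Section 12.3: "This safety plot will ensure a rapid reaction if TKM proves to be ineffective or harmful in the short term".
- **Timing of treatment.** Section 8.1 allows consent "anytime within 48 hours of first arriving at the ETC with a confirmed diagnosis", or within 48 hours of a positive PCR result for a patient already at the centre. Section 9.2 puts recruitment on the day of the first dose or one calendar day before it. Section 7.4 says that, whenever possible, "patient dosing will be started within 2 hours of the trial team arrival in the morning". Section 8.4 gives one dose a day for seven days.
- **Reactions.** Section 5.2 reports, in healthy participants given the parent compound TKM-100201 over one hour, a "transient inflammatory response that begins within 6 hours after infusion and dissipates in most cases by 24 hours post-dosing".

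**The concern.** The reason for the exclusion is a baseline one: some patients are too ill on arrival for any antiviral to help. The rule, however, is defined by an event that can follow treatment. A death on the day of the first infusion, or the day after, can be removed from S and n whatever caused it.

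This has two consequences. First, the plot cannot respond to early post-dose deaths, although Section 12.3 offers it as protection against short-term harm. Second, the primary probability p is conditional on surviving a period in which treatment may already have acted. A drug that brings deaths forward into the window raises p without saving anyone. A drug that delays early deaths beyond 48 hours lowers it.

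**Working it through.** **1. Can doses fall inside the window?** Assumptions, not in the documents: dosing at 10:00, admissions spread evenly over 24 hours, a 2-hour infusion. Let g be the hours from admission to the next 10:00, between 0 and 24.

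| First dose on | Dose 1 ends at | Share within 48 h | Dose 2 ends at | Share within 48 h |
|---|---|---|---|---|
| 1st morning | g + 2 | 100% | g + 26 | 22/24 = 92% |
| 2nd morning | g + 26 | 22/24 = 92% | g + 50 | 0% |
| 3rd morning | g + 50 | 0% | later | 0% |

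One dose inside the window is ordinary for a patient recruited promptly. Two doses require a start on the first morning. Late consent, or a PCR result after admission, can put every dose outside it.

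**2. Reproduce the plan's own figures.** The boundary in Figure 5 is not shown, so a straight line was fitted: check after every report, stop if S ≤ floor(0.682n − 4.854), maximum n = 100. It first stops at n = 8 with S = 0, as Section 12.7 says. Exact Bernoulli recursion gives the probability of claiming promising:

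| p | Table 4 | Fitted boundary |
|---|---|---|
| 0.50 | 0.002 | 0.0017 |
| 0.55 | 0.025 | 0.0249 |
| 0.60 | 0.158 | 0.1584 |
| 0.65 | 0.487 | 0.4866 |
| 0.70 | 0.827 | 0.8272 |
| 0.75 | 0.973 | 0.9725 |

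Table 4 is correct for p among 48-hour survivors. A second fitted line (0.685n − 5.1) agrees with it within about 0.003.

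**3. What the rule does when deaths only move earlier.** Start from the overall Table 3 estimate, 0.543, for a drug that saves nobody. Let h be the share of patients, among those who would otherwise have been counted, whose death by D14 is brought forward into the first 48 hours. The number of survivors is unchanged and the denominator shrinks, so plotted p = 0.543/(1 − h).

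| h (assumed) | Plotted p | P(promising) |
|---|---|---|
| 0 | 0.543 | 0.018 |
| 2% | 0.554 | 0.03 |
| 5% | 0.572 | 0.06 |
| 10% | 0.603 | 0.17 |
| 15% | 0.639 | 0.40 |

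The two fitted boundaries agree on these values to about 0.001. True survival in that group stays at 0.543 in every row.

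**4. What the four-patient safety cohort would see.** The chance of at least one such death among four patients is about 1 − (1 − h)^4: 0.08, 0.19, 0.34 and 0.48 for h = 2%, 5%, 10% and 15%.

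**The case against.** Several points on the other side stand.

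- **Dose timing is not fixed by the protocol.** A reader might infer that most patients have two doses inside the window. The documents do not say so; it follows only for prompt recruitment.
- **Onset is not death.** Section 5.2 describes a transient response in healthy participants and reports no deaths from it. A reaction to a dose given on the second day could also kill after 48 hours, and that death is counted.
- **The plot is not blind to harm in general.** A reader might infer that it cannot show short-term harm at all. Every death from 48 hours to D14 enters it, and that period covers most of the seven doses.
- **Other oversight exists.** The first four patients start in sequence and the IDMC reviews them before recruitment opens (7.4). A sign of cytokine response in that cohort triggers a recruitment review (8.7). Vital signs are checked up to 8 hours after each infusion (8.2). SUSARs go to the IDMC immediately, and suspected serious cytokine release goes to the operational group or the IDMC (11.2). All-allocated D14 mortality is a secondary outcome (Section 6). The IDMC charter is not shown and may add more. These are real safeguards, but none has a boundary. The reporting routes depend on judging relatedness, which Section 11 says will be very difficult.
- **The exclusion is deliberate and has a counterpart in Table 3**, which also omits early deaths. That is a good reason to keep it in the formal futility rule.

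A reader might also take a drug that kills 15% of allocated patients early, while the rest survive at 0.70, as proof of a false conclusion, since the plot still calls it promising with probability 0.83. It is not. Survival in all allocated patients would be 0.85 × 0.70 = 0.595, above the 0.543 benchmark, so the drug would be a net benefit. That case shows only that the plot does not register the early deaths.

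**Conclusion.** The concern holds as a blind spot. Early post-dose deaths are removed from S, n and the primary estimate, so the safety statement in Section 12.3 is not true for the first 48 hours after admission. It remains reasonable for later deaths.

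The size depends on h, for which the documents give no value. At 2% the chance of a false promising claim is about 0.03, close to the nominal 0.025. At 10% it is about 0.17 and at 15% about 0.40. These figures rest on a fitted boundary, on 0.543 as survival under an inert drug, and on 100 evaluable patients being reached if the boundary is not crossed. The direction does not depend on them: a death brought forward into the window can only raise plotted p.

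**What to change.** Keep the existing plot and exclusion as the formal futility rule. In Sections 12.1, 12.3 and 12.5, and in the IDMC charter:

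1. Add to each D14 report sent to the IDMC a second, descriptive tally of S and n in all allocated patients, leaving out only deaths before the first dose.
2. Notify the IDMC promptly of every death after a first dose, whatever the time since admission and whatever the relatedness judgement.
3. Report the primary estimate of p beside the estimate from the second tally.
4. Limit the safety statement in Section 12.3 to deaths after 48 hours, or attach it to the second tally.

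The cost is wording and one more line beside the existing plot. Allocations and D14 outcomes already reach the data management centre; the tally also needs the time of first dose and of death for early deaths. The drawback is that the second tally has no matched benchmark, because Table 3 leaves out deaths on the day of admission and the two days after. It can guide the IDMC but should not act as a stopping boundary against 0.55.
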